# Randomized controlled trial of enteral vitamin D supplementation (ViDES) in infants <28 weeks gestational age or <1000 g birth weight: study protocol

**DOI:** 10.1186/s13063-024-08274-8

**Published:** 2024-06-28

**Keywords:** Vitamin D, Extremely preterm infant, Randomized controlled trial, Bronchopulmonary dysplasia, Sepsis, Neurodevelopmental disorders, Osteopenia of prematurity, Bayesian analyses

## Abstract

**Background:**

Vitamin D is necessary to develop healthy lungs and other organs early in life. Most infants born before 28 weeks’ gestation have low vitamin D levels at birth and a limited intake during the first month. Enteral vitamin D supplementation is inexpensive and widely used. The appropriate supplementation regimen for extremely preterm infants is controversial, and the effect of different regimens on their blood levels and outcomes is unclear.

**Methods:**

Randomized, blinded comparative effectiveness trial to compare two vitamin D supplementation regimens for inborn infants <28 weeks gestation or <1000 g birth weight at a large academic center in the United States. Infants are stratified by birth weight and randomized within 96 h after birth to either routine supplementation (400 IU/day with established feedings) or increased supplementation (800 IU/day with any feedings) during the first 28 days after birth. We hypothesize that the higher and early vitamin D dose (800 IU/day with early feeding) compared to placebo plus routine dose (400 IU/day with established feeding) will substantially increase total 25-hydroxyvitamin D3 levels measured as state-of-art at 1 month, reduce respiratory support at 36 weeks’ postmenstrual age (on an ordinal scale predictive of later adverse outcomes), and improve or at least not worsen other important secondary outcomes. The infants in the study will follow up at 22–26 months’ corrected age (~2 years) with blinded certified examiners to evaluate neurodevelopmental outcomes. The sample size of a minimum of 180 infants provides >90% power to detect a >95% posterior probability of a 33% increase in serum 25-hydroxy vitamin D3 and >80% power to detect a >80% posterior probability of a relative risk decrease of 20% of reducing respiratory support by intention-to-treat Bayesian analyses using a neutral prior probability.

**Discussion:**

Our study will help clarify the uncertain relationship of vitamin D supplementation and its associated serum metabolites to clinical outcomes of extremely preterm infants. Confirmation of our hypotheses would prompt reconsideration of the supplementation regimens used in extremely preterm infants and justify a large multicenter study to verify the generalizability of the results.

**Trial registration:**

ClinicalTrials.gov NCT05459298. Registered on July 14, 2022.

## Introduction

### Background and rationale {6a}

Vitamin D is critical for many essential physiological processes. In early life, it is important for bone formation and calcium metabolism [1], regulation of immune and inflammatory responses [2], and development and maturation of the lungs (improving alveolarization, proliferation of vascular endothelial cells, and synthesis of surfactant) [3–5]. It may also have direct or indirect importance to brain development [6].

Because vitamin D is transferred mainly to the fetus during the third trimester, preterm infants are born with low vitamin D levels and stores [5, 7, 8]. In a recent meta-analysis, low vitamin D levels relative to current norms during infancy were identified in 70% of the preterm infants with a mean gestational age (GA) of 29 weeks [9]. During the first month after birth, low vitamin D levels persist in extremely preterm (EP) infants due to the low vitamin D content in human milk, prolonged or recurrent feeding intolerance common in EP infants, and administration of medications like caffeine and corticosteroids [10].

Unfortunately, the appropriate vitamin D supplementation for EP infants is uncertain, and vitamin D recommendations range from 200 to 1000 IU/day [11–13]. Supplementation with 400 IU/day as recommended by the American Academy of Pediatrics [12] is not likely to correct the vitamin D deficiency for EP at 4 weeks after birth by current norms. A recent cohort study of 301 infants (115 infants <1000 g birth weight [BW]), 80% had low 25-hydroxy vitamin D3 (25-OH-D_3_) level 4 weeks after birth, and the infants less than 1000 g did not develop sufficient serum levels of vitamin D until 12 weeks [14].

To our knowledge, only one clinical trial has compared lower (0–400 IU/day) and higher supplementation (800–1000 IU/day) in EP infants [5]. Although the differences in outcomes did not reach statistical significance, the findings with the higher supplementation regimen were compatible with a 28% reduction in bronchopulmonary dysplasia (BPD) or death at 36 weeks postmenstrual age (PMA) (relative risk [RR] 0.72 [95% CI 0.37–1.41]) and a 40% reduction in neurodevelopmental impairment (NDI) at 2 years (RR 0.60 [95% CI 0.3–1.2]) [5, 15].

While other potential benefits of higher dose vitamin D supplementation have not been adequately studied, a meta-analysis of 12 small trials identified a significant increase in length and head circumference and several measures of immune function when preterm infants were supplemented with 800–1000 IU/day compared to the 400 IU/day [16].

Appropriate supplemental vitamin D would be a low-cost nutritional intervention available worldwide that could reduce respiratory support, BPD, infections, osteopenia, poor growth, and/or NDI in EP infants, and the long-term adverse effects of these disorders for these babies and their families [17].

Additional clinical trials to assess increased vitamin D supplementation for EP infants are clearly needed, given the low cost of vitamin D, the wide variety of potential benefits, and the high prevalence of adverse outcomes in these infants.

We will analyze our single-center trial using conservative Bayesian analyses to directly assess the probability of clinical benefits from higher dose supplementation and to avoid the limitations of traditional frequentist analyses, particularly for studies with a limited sample size [18–22].

### Objectives {7}

The objectives are to determine if higher dose supplementation (800 IU/day with any feedings) compared to our routine supplementation regimen (400 IU/day with established feedings) for EP infants during the first 28 days after birth will:Increase the level of 25-OH-D_3_ 1 month after birth by more than 33%Reduce the need for respiratory support at 36 weeks’ PMA with a probability of more 80% (using the ordinal outcome described below and Bayesian analyses)Improve or at least not worsen other secondary outcomes (bronchopulmonary dysplasia; duration of respiratory support; hospital stay; infections; fractures; growth and development through 2 years; and death or individual morbidities)

### Trial design {8}

Randomized, blinded, parallel-group comparative effectiveness trial with a 1:1 allocation ratio. The trial is designed as a superiority trial.

## Methods: participants, interventions, and outcomes

### Study setting {9}

The study will take place at the neonatal intensive care unit (NICU) at Children’s Memorial Hermann Hospital in Houston, TX, one of the largest NICU in the US, with >1400 admissions and >100 infants <29 weeks’ gestation per year.

### Eligibility criteria {10}

Inclusion criteria: <28 weeks’ gestation (best obstetric estimate) or <1000 g BW; age <96 h at enrollment; inborn.

Exclusion criteria: GA ≥32 weeks; major anomaly; overt congenital nonbacterial infection; severe illness or immaturity that the attending neonatologist judges intensive care to be unjustified; or prenatal diagnosis of cystic fibrosis.

### Who will take informed consent? {26a}

Trained research personnel approach the mother or authorized legal guardian of eligible infants within 96 h after birth and provide a copy of the informed consent form, allowing sufficient time to make an informed decision.

### Additional consent provisions for collection and use of participant data and biological specimens {26b}

In the event of withdrawal from the study, the parents will be asked for their consent to continue the collection of electronic data. The consent form includes the collection of blood for vitamin D metabolites.

## Interventions

### Explanation for the choice of comparators {6b}

As may be typical [23], depending on their weight, age, and feeding tolerance, our patients in the routine care group receive a total vitamin D intake from all sources of ~160–600 IU/day during the first month after birth. Multivitamins, providing 160 IU/kg/day of vitamin D, are added to the parenteral nutrition from day 2 after birth. Almost all infants are fed human milk (mothers’ or donors’ human milk) that contains minimal vitamin D. When the infant tolerates 80 ml/kg/day, feedings are fortified up to 24 kcal/oz with bovine-derived human milk fortifier, and the parenteral multivitamins are discontinued. Enteral supplementation of 400 IU/day of vitamin D3 (cholecalciferol) is started when feedings reach ~120 ml/kg/day. We routinely increase fortified feedings to 160 ml/kg/day to support growth, providing ~190 IU/kg/day of vitamin D. Administering an inactive placebo (normal saline) is justified due to the uncertainty surrounding the optimal dosage of vitamin D supplementation for EP infants during the initial month after birth (Table 1).

**Table 1 Tab1:** Total vitamin D intake from all sources at various feeding intakes and times

**Vitamin D intake**	**60 ml/kg/day of UF** **≤28 days after birth**	**120 ml/kg/day of FF** **≤28 days after birth**	**160 ml/kg/day FF** **≤28 days after birth**	**160 ml/kg/day FF** **>28 days after birth**
**Routine care**	~160 IU/kg/day from PN + <3 IU/day from UF^a^ + placebo	~140 IU/kg/day from FF + 400 IU/day^b^ + placebo	~190 IU/kg/day from FF + 400 IU/day + placebo	~190 IU/kg/day from FF + 400 IU/day
**Intervention**	160 IU/kg/day from PN + <3 IU/day from UF^a^ + 800 IU/day (study drug)	~140 IU/kg/day from FF + 800 IU/day (study drug)	~190 IU/kg/day from FF + 800 IU/day (study drug)	~190 IU/kg/day from FF + 400 IU/day

*PN* Parenteral nutrition, *UF* Unfortified feedings, *FF* Fortified feedings

^a^Breast milk vitamin D content is minimal (~3 IU/100 ml). Fortification starts when the infant tolerates feeds of at least 80 ml/kg/day

^b^400 IU/day will not be started until the infant reaches 120 ml/kg/day of breast milk with human milk fortifier up to 24 kcal/oz (~140 IU/kg/day)

### Intervention description {11a}

The intervention group is supplemented with 800 IU/day with any feeding for the first 28 days after birth. The 800 IU/day is divided into 4 doses/day and are administered every 6 h with feedings to reduce osmolality and provide a more uniform intake that may be better tolerated, absorbed, and utilized [5] (Table 1).

### Criteria for discontinuing or modifying allocated interventions {11b}

Two independent blinded-to-treatment group investigators review the electronic medical records of the study infants daily during their admission to the NICU. The study drug will be discontinued if vitamin D toxicity is suspected, at the attending physician’s discretion, and for the period the infant is not receiving feeding during the intervention period.

### Strategies to improve adherence to interventions {11c}

Extensive education was provided before the study started. A laminated card with a QR code linking to study information and the team’s contact details is placed on the patient’s bedside. The research study closely monitors the patient to ensure protocol compliance. A missed dose can be given with the next feed, with a maximum of 2 doses together, and must be administered within 24 h. Before the vitamin D level collection, the research team calls the bedside nurse to provide a reminder of the blood sample collection time.

### Relevant concomitant care permitted or prohibited during the trial {11d}

No more than 400 IU/day of vitamin D enteral supplementation as part of routine care is allowed in any group during the first 28 days after birth. The infant will only receive the study drug (extra vitamin D or placebo) if receiving feedings. The blood collection for enrolled infants is only collected with usual laboratory testing, and no additional venipuncture for the study will occur.

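### From 120 ml/kg/day of feeds to day 28, the printed dose labels put a routine vitamin D order in the control arm only, which conflicts with the stated blinding

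*Protocol article*

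**What the plan says.** All places are in the Protocol article.

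- **Intervention description {11a}:** "The intervention group is supplemented with 800 IU/day with any feeding for the first 28 days after birth", and "The 800 IU/day is divided into 4 doses/day and are administered every 6 h with feedings". No reduction at any feed volume is stated.
- **Table 1, under Explanation for the choice of comparators {6b}, 160 ml/kg/day up to day 28:** controls have "190 IU/kg/day from FF + 400 IU/day + placebo" and the intervention arm has "190 IU/kg/day from FF + 800 IU/day (study drug", where the bracket then closes. The 120 ml/kg/day column follows the same pattern.
- **Text of {6b}, on unit practice:** "Enteral supplementation of 400 IU/day of vitamin D3 (cholecalciferol) is started when feedings reach ~120 ml/kg/day". On the control product: "Administering an inactive placebo (normal saline) is justified".
- **Concomitant care {11d}, for the period up to day 28:** "No more than 400 IU/day of vitamin D enteral supplementation as part of routine care is allowed in any group". On when the product is given, the same section says: "The infant will only receive the study drug (extra vitamin D or placebo) if receiving feedings".
- **Who will be blinded {17a}:** parents, ward staff and the research team are said not to know the arm. Only the statistician and the investigational pharmacy do. Placebo and study vitamin D are matched for volume and appearance.

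**The concern.** The matching described in {17a} covers the study product: active drops against saline. It does not cover a second, routine vitamin D order. If Table 1 is followed as labelled, a control infant who reaches 120 ml/kg/day before day 28 gets such an order and an intervention infant does not, so anyone reading the chart can tell the arm. Section {11b} has two blinded investigators reviewing that chart every day, and {13} has vitamin D intake taken from it.

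Two things are at stake. The first is blinding for outcomes that staff decide or measure. The second is a clear statement of the dose in each product, which anyone repeating the regimen in the multicenter trial that the Discussion of the abstract foresees would need.

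**Working it through.** **1. Check Table 1 against the article's own total.** The article gives about 160–600 IU/day from all sources under routine care. Assume a weight of 1 kg. Parenteral nutrition alone gives 160 × 1 = 160 IU/day. At 160 ml/kg/day of fortified feeds, a control gets 190 × 1 + 400 = 590 IU/day. Both ends agree. The controls' 400 IU/day is therefore a real dose, counted separately from the saline.

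**2. Locate the window.** In the 60 ml/kg/day column neither arm has a routine enteral dose, so the arms differ only in the matched product. After day 28 both arms have the same 400 IU/day. The conflict runs from 120 ml/kg/day to day 28.

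**3. Set out the possible arrangements in that window** (enteral supplement, IU/day).

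| Arrangement | Intervention | Control | Difference | Visible orders | Printed statement it contradicts |
|---|---|---|---|---|---|
| A. Routine 400 in both arms, study drug stays at 800 | 800 + 400 = 1200 | 400 | 800 | Same | Every stated total of 800 |
| B. Routine 400 in controls only | 800 | 400 | 400 | Differ | Blinding in {17a} |
| C. Routine 400 in both arms, study drug cut to 400 | 400 + 400 = 800 | 400 | 400 | Same | Study-drug label in Table 1; {11a} |
| D. Control 400 inside the masked product | 800 | 400 | 400 | Same | Saline placebo plus separate routine dose |

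B is Table 1 read literally. C and D keep both dose and blinding, but each makes a printed label wrong.

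**4. See which outcomes B would expose.**
- *While orders differ:* steroid treatment to lower respiratory support, and duration of support ({12}).
- *Just after:* length and head circumference at 1 month, measured by the research team ({18a}).
- *At 36 weeks' PMA (252 days):* the orders have been the same since day 28. The gap is 252 − 154 − 28 = 70 days for birth at 22w0d and 252 − 195 − 28 = 29 days at 27w6d. For infants under 1000 g born at 28w0d to 31w6d it is 252 − 196 − 28 = 28 days down to 252 − 223 − 28 = 1 day.
- *25-OH-D3:* measured by mass spectrometry ({18a}), so not open to observer judgement.

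**5. Check whether the power figures depend on this.** Inputs from {14}: mean 25, SD 12, true increase 33%, so a difference of 0.33 × 25 = 8.25 ng/ml. With a one-sided 5% test as the flat-prior equivalent of a posterior probability above 95%, and 90% power, the result is 37 per arm, 74 in total, power 0.905. This reproduces the stated 74. No input is a product label or an order.

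**The case against.** **Section {11d} is only a ceiling.** Giving no routine vitamin D in the intervention arm complies with it. This stands. The conflict is between the dose labels and the blinding claim; {11d} merely fails to resolve it.

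**The text points to a coherent scheme.** Sections {11d} and {13} call the study drug extra vitamin D, the trial's name says extra supplementation, the abstract describes the comparator as placebo plus the routine dose, and Table 1 is titled as total intake. Together these suggest a blinded top-up on routine care, which is arrangement C. This stands as the likely intent. It does not rescue the print, because under C the study drug from 120 ml/kg/day is 400 IU/day, whereas Table 1 labels all 800 as study drug and {11a} divides 800 into four doses.

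**An article may leave dispensing detail to the full protocol.** That is true of missing detail. Here the statements that are printed conflict, and if the full protocol uses C or D, the article's labels are wrong.

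**Stronger readings that the documents do not support.** A reader might infer that intervention infants receive 1200 IU/day. The abstract, the objectives, Table 1, {11a} and the Discussion all give 800, and {11d} orders nothing. As a hypothetical only, take study drug on days 5–28 (24 days) without interruption, so 800 × 24 = 19,200 IU, and 120 ml/kg/day reached at day 7, 14 or 21. These ages are assumed; the article gives none. Controls receive 400 × (28 − T) = 8,400, 5,600 or 2,800 IU. The printed cumulative contrast is 10,800, 13,600 or 16,400 IU, against 19,200 under arrangement A, a ratio of 1.78, 1.41 or 1.17. The high figure needs feeds of 120 ml/kg/day by day 7, in a population the article describes as prone to feeding intolerance.

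A reader might also infer that the trial has in fact been unblinded, or that the benefit stopping rule on the 36-week ordinal outcome is compromised. The article does not say how the control dose is ordered or charted. The 36-week outcome could be reached only through remembered allocation or old chart entries.

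**Conclusion.** The point holds as a conflict between printed statements. From 120 ml/kg/day to day 28, Table 1 and {11a}, taken literally, leave a routine order in controls only, and {17a} does not cover that. The likely intent is a total of 800 versus 400 IU/day. A total of 1200 IU/day is a possible misreading that {11d} leaves open, and is not the stated dose.

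The size of any bias cannot be computed from the documents. It arises only if the control dose is an open order that staff can recognise. It is then limited to secondary outcomes open to judgement: steroid treatment, duration of respiratory support, and length and head circumference at 1 month. The assayed primary outcome and the sample-size figures are unaffected. The conflict is worth correcting because the correction is cheap and settles both the blinding and the dose in each product.

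**What to change.** Amend Table 1, {11a} and {11d} so that visible vitamin D orders are identical in both arms up to day 28 and the intervention enteral supplement is capped at 800 IU/day in total. Either of these does it:

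1. From 120 ml/kg/day, give an open routine 400 IU/day in both arms, with the blinded active product cut to 400 IU/day at the same volume and controls on saline.
2. Have no open routine order before day 28, and give the control 400 IU/day inside the matched blinded product from 120 ml/kg/day.

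If one of these is already the practice, correct the labels to say so. In either case, state which practice has been followed since enrollment began in September 2022, and report actual vitamin D intake by arm beside the primary result. Intake is already collected under {13}.

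**Cost.** If practice already matches, this is a wording correction. If practice must change, it is a protocol and pharmacy-procedure amendment with no new patients, samples or data items. The pharmacy must then be told when feeds reach 120 ml/kg/day and must dispense a second preparation. Under {25} a change applies only to infants enrolled after it, so those already enrolled stay under the earlier practice. From September 2022 to publication at the end of June 2024 is about 22 of the roughly 34 months to the planned end of recruitment in July 2025, so at most about the last 12 months of recruitment could be changed.

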### Provisions for post-trial care {30}

Infants will be provided with comprehensive care in the high-risk follow-up program that includes treatment for acute and chronic illnesses from subspecialists and primary care providers available in the clinic 40 h per week and by telephone at all hours. This program includes multiple measures to promote prompt and effective outpatient and inpatient care, and it has been shown in randomized trials to increase parent satisfaction, achieve high follow-up rates, and reduce serious illnesses (prolonged hospitalizations, pediatric intensive care unit admissions, or death) [24, 25].

### Outcomes {12}

The primary outcome is 25-(OH)D_3_ levels at 1 month after birth.

The secondary outcomes are indicators of likely or plausible effects of vitamin D supplementation on the function or structure of the lungs, bones, immune system, and brain, including:Respiratory support required at 36 weeks PMA using an ordinal scale (Table 2).Duration of respiratory support up to 2 years corrected age (CA), steroid treatment to decrease respiratory support, pulmonary hypertension at 36 weeks PMA, and wheezing at 2 years.Weight, length, and head circumference at birth, 1 month, 36 weeks’ PMA, and at 2 years’ CA. Fractures identified before NICU discharge and up to 2 years of CA. Serum calcium, phosphorus, and alkaline phosphatase levels during the first 28 days after birth and at 36 weeks’ PMA.Bayley™ Scales of Infant and Toddler Development, fourth edition (BSID-IV) neurodevelopmental assessments and NDI at 2 years’ CA.Hospital-acquired sepsis, length of stay, and readmissions.Serum concentrations of 25-OH-D_3_, 25-OH-D_2_, 3-epi-25-OH-D_3_, and 24,25-(OH)_2_D_3_ by liquid chromatography-tandem mass spectrometry.

**Table 2 Tab2:** Ordinal respiratory outcomes

**No BPD**	**Grade 1 BPD**	**Grade 2 BPD**	**Grade 3 BPD**	**Death**
No respiratory support	NC ≤ 2 L/min	NC > 2 L/min, non-invasive ventilation	Intubated mechanical ventilation	Death before 36 weeks PMA

*NC* nasal cannula

Severity graded according to the mode of support at 36 weeks PMA, irrespective of oxygen supplementation needs

Other outcomes are important differences between groups in other major clinical diagnoses are unexpected with our sample size and will be considered hypothesis-generating. We will report grade III–IV intraventricular hemorrhage, periventricular leukomalacia, surgically treated necrotizing enterocolitis, spontaneous intestinal perforation, stage III–V retinopathy of prematurity, and patent ductus arteriosus.

